**A4 Proposed start date and duration in months**

In giving a date please bear in mind the timescale for decision-making by SCC, the Ethical Committee and any other institutions whose agreement is needed, and the time needed to organise the resources required.

September 2001, for 3.5 months at Farafenni; data analysis to follow in London and The Gambia.

NB. This study follows that of 2000 by the same investigators, in which we measured post-treatment transmission among children treated with chloroquine plus artesunate.

**A5 Reference (office use)**

**Scientific Co-ordinating Committee No Project #887**

**Ethical Committee No #887**

**A6 Summary of project, long term objectives and specific aims (not more than 200 words)**

This section is very helpful to the Committees in determining quickly the main features of the study, and should be as clear and concise as possible. It should cover the key objectives and endpoints and, if the project is hypothesis driven, then the hypothesis should be stated here.

Widespread resistance of *Plasmodium falciparum* to commonly-used drugs has lead to the formulation and testing of new combinations of anti-malarials, particularly those including one of the artemisinins. This proposal is one in a series of trials aimed at identifying drug combinations that reduce or prevent post-treatment transmission of *P. falciparum*. Our studies in 1998/9 have shown that:

- Sulphadoxine/pyrimethamine (SP; Fansidar®) treatment is followed by high gametocytaemia in a large proportion of subjects.
- Compared to SP, artesunate + SP reduces, but does not prevent, transmission of *P. falciparum* to mosquitoes.

Further, preliminary analysis of our 2000 trial suggests that:

- the prevalence of resistance to chloroquine is sufficiently high in The Gambia to severely compromise chloroquine + artesunate as a treatment for uncomplicated malaria.
- chloroquine + artesunate reduces transmission at day 7, but this benefit is probably transient, as gametocyte carriage increases significantly in the latter half of follow-up.

Thus whereas both of the artesunate combinations we have tested do reduce the infectiousness of treated children, neither can completely prevent transmission. It would be very useful to know whether the commonly used combination of chloroquine and sulphadoxine-pyrimethamine (SP, Fansidar) can also reduce transmission. We propose to test the infectiousness of children treated with chloroquine and SP as in The Gambia this combination has been shown to be a more effective treatment for symptomaticmalaria than SP alone (13) and is currently the recommended treatment for complicated malaria (14). However gametocyte prevalence, density and transmissibility to mosquitoes have not been systematically measured in patients treated with chloroquine and SP. We would also include treatment arms of both PS and CQ alone.

This protocol fits well with the overall research aims of our programme of research, and has the added benefit that the drugs concerned are low cost and already available in The Gambia. This combination may thus be considered as a possible alternative to the current front-line therapy of CQ alone.

#### A7 Checklist/Signatures

**Please complete the following checklist and comment as appropriate.** This section is designed to ensure that all the planning steps have been taken that are needed for successful project. For projects at the MRC Laboratories, Programme Heads will help visiting workers, and others preparing proposals at a distance, to ensure liaison with key individuals who need to be consulted locally.

1. **Has the project been discussed and cleared with the institutions in which research will be carried out including health services to which the study will need access?**

Yes

1. **Have all investigators and collaborators given their agreement to take part in the study as described?**

Yes

1. **Has a CV been attached for the principal investigator if unknown to the Committee?**

Not applicable

1. **Have ethical issues been addressed? Give details in section C.**

Yes

1. **Have safety issues been addressed? Please give details**

Yes

1. **Will the project require data and/or materials to be taken out of The Gambia? If so please give details** Data will be analysed at LSHTM in collaboration with MRC staff in The Gambia. We plan to take the following material out of The Gambia to either LSHTM or the University of Edinburgh (*):

- filter-paper blood spots for genotyping studies
- small (~50l) blood samples for RNA extraction *
- alcohol-fixed oocysts from mosquito guts
- frozen sera used in transmission experiments
- paraformaldehyde-fixed parasites on microscops slides for immunofluoresence*

1. **For projects to be carried out at MRC Laboratories: Have the following been consulted about the support services, resources and working space required?**

|  | **Consulted: Yes/No/Comment** |
| --- | --- |
| Laboratory Manager (including safety issues) | Ongoing |
| Director of Clinical Services | Project at AFPRC hospital/MCH clinic, discussed with CE hospital, and DHT |
| Head of Computing | Data-entry at Farafenni field station, overseen by [name] |
| Transport Manager | Ongoing |
| Finance Manager | Ongoing |
| Personnel Manager | Not available |
| Administrative Director | Not available |
| Other services – specify | Modest requirement for printing forms to be done at Farafenni |

**Signature of principal investigator: Date:**

**__________________________________________________________________________**

**B Description of Project**

**B1 Background**

In response to the widespread occurrence of chloroquine-resistant parasites in Africa, and the more recent demonstrations that resistance to sulphadoxine/pyrimethamine (SP) is reducing the efficacy of that drug (6,8), calls have been made for the deployment of new effective antimalarial combinations. Of particular interest are the artemisinins, which have short elimination half-lives, in various combinations with longer-acting drugs (11,12). Recent trials of artesunate in combination with SP in Africa have shown this to be a safe and efficacious regimen (9,10), but that a certain level of post-treatment transmission occurs (7,10). It is of importance to determine the effects of the artemisinins on *P. falciparum* transmission, and to use this information in the formulation of appropriate combination therapies for use in Africa.

We have run a series of trials in which we can measure *P. falciparum* gametocyte prevalence, density and infectivity to mosquitoes after treatment with artemisinins in various combinations with other anti-malarials. This work has been carried out at the MRC field station at Farafenni, The Gambia, during three consecutive malaria transmission seasons (1998 and 1999; ref. 7; 2000, [name] et al., unpublished). In total 1,636 children have been treated with either chloroquine alone, chloroquine plus artesunate, SP alone, or SP plus artesunate.

## Our studies in 1998/9 showed that artesunate, in combination with SP, reduced both the mean density of gametocytes in positive subjects, and the prevalence of gametocytes in the treated population (7) compared to SP alone. Nevertheless, a gametocyte prevalence of 5-10% was observed at day 7 in the combination group, and these gametocytes were capable of infecting mosquitoes in membrane-feeding experiments (7). Therefore, there may still be considerable transmission after treatment with artesunate combined with SP.

In 2000, we compared treatment with the combination chloroquine plus artesunate (3 days) with chloroquine alone. We have not completed analysis of this trial yet, as a duplicate slide-read is currently ongoing, but the following summary of our preliminary findings can be made:

- parasitological treatment failures with chloroquine alone were very common, the cumulative rate at day 28 approaching 60% (although this is a crude figure which includes re-infections)
- parasitological treatment failures with chloroquine plus artesunate were also unacceptably high, with a cumulative rate at day 28 of 39%, although on average these occurred much later in follow-up that failures with chloroquine alone.
- Clinical failures mirrored this pattern, with cumulative failure rates by day 28 of 12% and 8% respectively. The addition of artesunate to chloroquine treatment significantly reduced the probability of a child returning with clinical malaria within 14 days of treatment, but this benefit was not observed in the latter half of follow-up.
- Gametocyte carriage was significantly reduced in the combination group up to day 14, but day 28 gametocyte carriage rates were high in both groups: 34% for chloroquine and 21% for chloroquine +artesunate.
- Children identified as gametocyte carriers on day 7, but who were gametocyte-negative on admission, were tested for infectiousness to *Anopheles*. Some gametocyte-carriers from both groups were infectious (12/26 for the chloroquine group; 4/17 for the combination group), although gametocytes from children receiving chloroquine plus artesunate were less infective.

We conclude from this preliminary analysis that whereas addition of artesunate to chloroquine does reduce transmission immediately post-treatment, the emergence of asexual and sexual parasites in the 3rd and 4th weeks greatly reduces this benefit over the longer term.

Since none of the combinations so far tested are ideal to reduce transmission and it is important to know if they are superior to the commonly used combination of chloroquine and sulphadoxine-pyrimethamine (SP, Fansidar). We propose to test the infectiousness of children treated with chloroquine and SP as in The Gambia this combination has been shown to be a more effective symptomatic treatment than SP alone for malaria (13) and is currently the recommended treatment for complicated malaria (14). However gametocyte prevalence, density and transmissibility to mosquitoes have not been systematically measured in patients treated with chloroquine and SP. We would compare the results with those obtained among groups of children treated with CQ alone and with SP alone.

This protocol fits well with the overall research aims of our programme of research, and has the added benefit that the drugs concerned are low cost and already available in The Gambia. This combination may thus be considered as a possible alternative to the current front-line therapy of CQ alone.

In all our studies to date, we have examined gametocyte infectivity by feeding mosquitoes either 4 or 7 days after treatment. Our parasitological data show that gametocytes persist, particularly after SP treatment, for up to 3 weeks beyond this point (7). These persistent circulating gametocytes may no longer be fully viable. However, if they are infective they could represent a significant source of further transmission, due to the lengthy time period during which they are available for mosquitoes to ingest them. The Wellcome Trust grant review panel strongly suggested that this question be incorporated into our study design within the period of the grant. For this reason, we intend to stagger the gametocyte screening process among those children that receive SP to examine the relative infectivity of gametocytes isolated 7, 10 or 14 days following treatment.

### B2 Project description

Primary aim:

- To measure *P.falciparum* transmission after chloroquine and SP vs either treatment alone.

Secondary aims:

- To measure the duration of infectivity of gametocytes isolated from SP-treated children.
- To measure the genetic complexity of gametocyte populations
- To measure the prevalence of alleles associated with drug resistance

**Specific objectives:**

1. Using a randomised control trial (RCT) design, measure the transmission potential of Gambian children after treatment with anti-malarial drugs alone and in combination. Using gametocyte prevalence, density and infectivity to mosquitoes as outcome measures, we plan to test whether chloroquine and SP effectively reduces transmission compared to either treatment alone and, by comparison with our previous work, compared to combinations including artesunate. To do this, we will set up a randomised control trial of chloroquine and PS versus groups treated with either PS or chloroquine.
2. Measure infectivity in a staggered group of gametocyte isolates, collected at day 7, day 10, and day 14 after SP treatment. This is because our studies to date have not enabled us to estimate the duration of infectivity of gametocytes that appear after drug treatment.
3. Examine genetic complexity of gametocyte populations *in vivo* by PCR analysis of polymorphic loci, and use RT-PCR of peripheral blood RNA to establish stage specificity of parasite samples. We will further develop these techniques in collaboration with [name] and [name] (1).
4. Use PCR genotyping at putative drug-resistance loci, in combination with data on treatment failures, to estimate the prevalence of resistant parasites in the emerging gametocyte population. Oocysts from infected mosquitoes will also be typed. Quantification of the relative contribution of different genotypes to circulating gametocyte pools will be estimated using the *in situ* PCR approach recently developed by our collaborators [name] and [name] (5).

**Experimental Design and Methods to be Used**

###### Clinical trial and transmission experiments

Over the three previous seasons, we have established a randomised control trial (RCT) protocol, modified from the standard WHO guidelines for efficacy trials, for the examination of post-treatment transmission of falciparum malaria.

Children aged 1-10 years attending the Farafenni AFPRC Hospital and MCH clinic requiring treatment for uncomplicated malaria will be recruited into the study after appropriate consent has been obtained from a parent or guardian. They will be randomly assigned to a treatment group by clinicians of the MRC Station, Farafenni. Clinical and demographic data will be recorded on a standardised case report form (CRF) as in previous years. The principal investigator and entomologists will be blinded as to the treatment group of each child. Field workers will be required to monitor drug doses on days 2 and 3 in the child’s home and therefore cannot be blinded. Blood films, blood spots and a microtainer blood sample will be obtained at the time of treatment. The blood sample will be used to measure PCV, genotyping parasites and previous chloroquine intake.

All subjects will be actively followed up at home for two weeks on either days 7 or 10, and on days 14 and 28 post-treatment. Parents and guardians will be encouraged to bring the child back to the clinic at any other time the child is unwell. On one follow-up day (7, 10 or 14) the child and a guardian will be brought to the field station for gametocyte screening. On each occasion, 2 thick films will be taken, and blood spotted onto filter paper for genotyping. On the gametocyte screening day, the child will be asked to remain at the field station until one thick film has been read. If gametocytes are present, and permission given, 2 to 3 ml of blood will be taken by venupuncture and immediately processed for mosquito infection studies.

Farafenni has two purpose-built insectaries. We plan to use this protocol for the next two consecutive transmission seasons at Farafenni for comparative studies of post-treatment malaria transmission. Currently we are breeding F1 generation *Anopheles gambiae* from wild caught mosquitoes for these experiments but it is a priority in the coming season is to establish a stable colony of *A. gambiae* in the Farafenni insectaries.

In our 1998, 1999 and 2000 trials based at the Farafenni Health Centre we recruited 600 children over 15 weeks, 500 children over 10 weeks, and 536 children over 9 weeks respectively. These rates of subject recruitment, combined with gametocyte prevalence data from each year will be fed into the study design to ensure sufficient mosquito feeds across the treatment groups.

We will analyse the results of the trial for all the relevant clinical, parasitological and entomological parameters available to us. In addition, we have used two summary statistics (the probability of post-treatment infectiousness, and the infectious proportion of subjects) that incorporate gametocyte prevalence, density and infectivity to mosquitoes (7). These data will then be related to the estimated proportion of treated infections in rural areas of The Gambia to derive an estimate of the contribution that children treated with each regimen would make to transmission.

###### Parasite genotyping

We intend to establish the necessary capacity to perform basic molecular biology in the laboratories at Farafenni. Along with our collaborators at Edinburgh University, we have secured funding for a PCR machine and electrophoresis equipment from the Gates Malaria Programme at LSHTM, and the MRC. We have also obtained sufficient funding to support a higher scientific officer with experience in molecular biology. She/he will be trained in the specific techniques used in these studies and be responsible for these aspects of the work in the field station.

We propose to measure the genetic complexity of gametocyte populations in individuals, and to relate this to the genetic complexity of oocysts in mosquitoes fed on those individuals. This will permit us to track longitudinally the movement of drug-resistant alleles from asexual parasites, to gametocytes, to mosquitoes. From blood spotted on filter paper, we have been able to use PCR genotyping of the polymorphic single locus genes encoding MSP1, MSP2 and GLURP to elucidate the genetic complexity of circulating gametocytes. We prefer to use antigen-encoding loci for this purpose rather than “neutral” markers such as micro-satellites because of their greater within-population diversity, which provides better resolution among genotypes.

A novel application of RT-PCR has allowed us to detect expression of developmental stage-specific genes in peripheral blood obtained at the time of feeding mosquitoes ([name] *et al.,* in preparation). RT-PCR of an asexual-specific locus (*resa*) and a gametocyte-specific locus (*pfs16*) permits samples with gametocytes only and samples with sub-patent asexual parasites as well to be distinguished from each other. Thus we can clarify whether the DNA in our genotyping experiments is derived from gametocytes only, or from a combination of gametocytes and asexual parasites at the limit of detection of our RT-PCR system. These techniques are complementary to those of our collaborators [name] and [name] (1). The results of this molecular genetics approach have clearly demonstrated that day 4 and day 7 circulating gametocytes comprise a mix of, on average, two or more genotypes. Thus in our study area the requirements are being met for heterologous genetic recombination to occur in the mosquito. This is the first time such an analysis has been reported. However, this work included only 10% of our study subjects, and a meaningful comparison among treatment groups was not possible with this sample size. We plan an expansion of this work to other drug treatment groups, and with larger sample sizes, using these methodologies.

We propose to determine the genotype of our samples at loci involved in drug resistance. We will type at both the *dhfr* and *dhps* loci implicated in resistance to SP. These analyses will provide crucial information as to the contribution of drug-resistant loci to the emerging gametocyte pool, and thus give much-needed empirical data concerning the rate of increase of the prevalence of drug resistant genotypes in African parasite populations. Further, using the combination of chemotherapy trials with mosquito infectivity studies, we will be able to follow drug-resistant genotypes into the mosquito, by dissecting oocysts from infected mosquitoes and typing them with established PCR methods (2-4). Thus we will have longitudinal genetic typing data from 3 life-cycle compartments originating from a single infection: asexual parasites (taken at the time of clinical presentation), gametocytes (taken at day 7 after treatment has largely removed the asexual parasites) and oocysts from the mosquito.

Using DNA prepared from filter paper blood spots we will use PCR to amplify candidate loci, particularly *pfcrt*, *pfmdr1*, *dhfr* and *dhps*. These results will be correlated with both clinical data (i.e. which subjects failed treatment), and parasitological data (i.e. which subjects had persisting patent asexual parasitaemias after treatment). This will enable us to build up a comprehensive picture of the prevalence of drug resistance alleles in emerging gametocyte populations in the field after drug treatment. The technique of *in situ* PCR, to be performed in collaboration with [name] and [name], will enable us to evaluate the relative abundance of gametocytes carrying drug-resistance loci in our gametocyte samples prior to feeding to mosquitoes. The subsequent typing of single oocysts from mosquitoes successfully infected with those same gametocytes will then allow us to evaluate the post-transmission abundance of these same loci.

1. Babiker, H. A., Abdel-Wahab, A., Ahmed, S., Suleiman, S., Ranford-Cartwright, L.C., Carter, R. and Walliker, D.1999. Detection of low level *Plasmodium falciparum* gametocytes using reverse transcriptase polymerase chain reaction. *Mol. Biochem. Parasitol.* **99:** 143-148.
5. Ranford-Cartwright, L.C., and Walliker, D. 1999. Intragenic recombinants of *Plasmodium falciparum* identified by in situ polymerase chain reaction *Mol. Biochem. Parasitol.* **102:** 13-20.

**B3 Details of study design and investigations**

1. **What type of study design is proposed (eg case control, prospective cohort, randomised controlled trial, descriptive etc)**

Randomised Control Trial

1. **What is the proposed size of the study (this may relate to patients, cases, controls, survey subjects, laboratory samples etc, as appropriate).**

The aim is to recruit approximately 500 patients, to have a minimum of 25 individuals per group who provide a blood sample for membrane feeding.

1. **Please describe the statistical considerations and sample size calculations involved in determining the size of the study.** (If you do not have access to statistical advice, please consult the MRC Laboratories Statistics Department.)

Approximately 500 patients will be treated. In our previous studies the observed gametocyte carriage rate 7 days after treatment with SP was >70% (excluding those who had gametocytes on day 0), and 40% after treatment with CQ. We therefore expect that the rate after SP + CQ will be at least 28% (ie 40% x 70%). Therefore, to ensure that at least 30 mosquito feeds are performed in each treatment group, we will aim to enrol **a)** 200 subjects in the CQ + SP group, **b)** 50, 60 and 70 subjects in the 3 groups receiving SP and being screened for gametocytes on days 7, 10 and 14 respectively, and **c)** 130 subjects in the CQ group. All CQ- and CQ + SP-treated children will be screened for gametocytes on day 7 only. This will provide sufficient power at the 90% confidence level to detect a 10-fold difference in infectiousness at day 7 between gametocyte-positive children treated with SP alone, and those treated with SP + CQ.

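### The 28% carriage rate for CQ + SP is an independence assumption, not a minimum, so 200 children do not ensure 30 mosquito feeds

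*Protocol*

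**What the plan says.** The sample size answer in B3 starts from the investigators' earlier trials: "gametocyte carriage rate 7 days after treatment with SP was >70% (excluding those who had gametocytes on day 0"), "and 40% after treatment with CQ". From these two rates it derives the combination rate: "We therefore expect that the rate after SP + CQ will be at least 28% (ie 40% x 70"%). The enrolment figures follow as a consequence, "to ensure that at least 30 mosquito feeds are performed in each treatment group": "200 subjects in the CQ + SP group", "50, 60 and 70 subjects in the 3 groups receiving SP and being screened for gametocytes on days 7, 10 and 14 respectively", and 130 in the CQ arm. CQ and CQ + SP children are screened on day 7 only. The paragraph ends with a power claim for a 10-fold difference in infectiousness at day 7 between gametocyte-positive children given SP and those given SP + CQ.

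Three other places bear on this:

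- The preceding B3 answer on study size sets a lower target: "to have a minimum of 25 individuals per group who provide a blood sample for membrane feeding".
- The methods text on the clinical trial and transmission experiments takes venous blood for feeding only when the film read that day shows gametocytes and permission is given.
- The summary (A6) and background (B1) both say that gametocyte carriage after CQ + SP has not been studied systematically.

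**The concern.** Multiplying two carriage rates gives the joint rate under independence. That is a point guess, and calling it a minimum needs a further argument that the protocol does not make. The largest arm (200 of 510 planned children) is sized on this figure, and the word *ensure* tells the committees that the feed count is secure.

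The exposure runs in an awkward direction. Objective 1 reads "we plan to test whether chloroquine and SP effectively reduces transmission compared to either treatment alone", with gametocyte prevalence among the outcomes. The better the combination suppresses gametocytes, the fewer carriers remain to feed from, so the infectivity comparison is thinnest where the treatment works best. The closing power claim concerns gametocyte-positive children only, so it depends directly on the feeds that this arm yields.

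**Working it through.** **Inputs, all from B3.** Day-7 carriage is above 70% after SP and 40% after CQ. Arms screened on day 7 are CQ + SP 200, CQ 130 and SP 50. The target is 30 feeds per group. The carrier-to-feed yield is not stated, so it is treated below as an assumption and shown over a range. Rates are applied to all enrolled children, as the plan does.

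**1. The plan's figure.** 0.40 × 0.70 = 0.28. It reproduces exactly.

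**2. Is it a minimum?** If the SP rate is above 70% and the effects are independent, the product is above 28%, so *at least* has a basis under independence. Without independence it has none. Take one simple model, in which a child carries under CQ + SP only if that child would carry under each drug alone. Marginal rates of 40% and 70% then allow a joint rate as low as 0.40 + 0.70 − 1 = 0.10 and as high as 0.40. Positive dependence puts the rate above 28%, negative dependence below. This shows only that 28% is not a floor. The limits belong to that model, and an interaction between the drugs could take the rate outside them.

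**3. Does 200 follow from 28% and 30 feeds?** If every carrier is fed, 30 / 0.28 = 107.1, so 108 children suffice. With 200 there are 200 × 0.28 = 56 carriers. The yield at which each arm gives exactly 30 feeds is:

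- CQ + SP: 30 / 56 = 53.6%
- CQ: 30 / (130 × 0.40) = 30 / 52 = 57.7%
- SP, day 7: 30 / (50 × 0.70) = 30 / 35 = 85.7%

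The three differ, so no single yield explains the arm sizes.

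**4. Feeds from 200 children.** Expected feeds = 200 × rate × yield. The chance of at least 30 is the exact upper tail of a binomial (200, rate × yield). Each cell shows expected feeds, then that chance.

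| Carriage | Carriers | Yield 100% | Yield 85.7% | Yield 57.7% | Yield 53.6% |
|---|---|---|---|---|---|
| 10% | 20 | 20; 0.016 | 17.1; 0.002 | 11.5; <0.001 | 10.7; <0.001 |
| 15% | 30 | 30; 0.53 | 25.7; 0.21 | 17.3; 0.002 | 16.1; 0.001 |
| 20% | 40 | 40; 0.97 | 34.3; 0.81 | 23.1; 0.08 | 21.4; 0.04 |
| 28% | 56 | 56; >0.999 | 48.0; 0.999 | 32.3; 0.70 | 30.0; 0.53 |
| 40% | 80 | 80; >0.999 | 68.6; >0.999 | 46.2; 0.998 | 42.9; 0.992 |

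**5. Break-even.** With every carrier fed, 30 feeds are expected at 30 / 200 = 15% carriage, and a 95% chance of at least 30 needs about 19%. At 28% carriage, a 95% chance needs a yield of about 0.192 / 0.28 = 69%.

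**The case against.** The best reply has four parts.

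- **The wording has a basis.** The SP rate is given as above 70%, and the sentence reports an expectation. Under independence *at least* is correct. This stands, but it moves the weight onto independence, which is unstated.
- **There is real slack.** 200 is nearly twice the 108 needed at 28% if every carrier is fed. Against the lower target of 25 feeds, break-even falls to 25 / 200 = 12.5%. The methods text also says that past recruitment and prevalence data will feed into the design to secure enough feeds. The slack stands, but it depends wholly on the yield, and at 54% it is used up.
- **Low carriage would not sink the trial.** Prevalence is itself an outcome. If carriage were 10%, 20/200 against an expected 52/130 on CQ gives z = 0.30 / 0.0465, about 6.4. This stands: the loss falls on infectivity among carriers.
- **A combination rate far below 28% is conjecture.** The background's 5–10% day-7 carriage under SP + artesunate concerns a different partner drug. It shows that a combination can fall well below SP alone and does not predict CQ + SP.

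A reader might also infer a low yield from the 26 CQ-group carriers tested in 2000. The protocol does not support that. It gives no size for that arm, does not say the 40% is the 2000 rate, restricts those tested to children gametocyte-negative on admission, and does not say what limited the number fed.

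**Conclusion.** The point holds as one about an unsupported minimum and an unsupported guarantee. The multiplication is right; the label on it is not. The 28% is a point assumption of independence for a combination whose carriage the protocol says is not systematically known. Even if 28% is right, 30 feeds are secure only at a carrier-to-feed yield that the plan does not state: the chance of reaching 30 is 0.53 at the yield that makes 200 the matching number and 0.70 at the yield implied by the CQ arm. At 20% carriage and that CQ-arm yield it is 0.08.

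These probabilities assume children are independent and that the implied yields are what the planners had in mind; the yields are back-calculated, not documented.

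Two stronger readings go too far. A reader might infer that the feed target will be missed. With high yield it is met down to carriage of about 15–19%, and positive dependence would raise carriage above 28%. A reader might also take 10% to 40% as the true range for carriage. Those limits hold under one joint-carriage model only. Nor can the power claim be called wrong on this ground: B3 gives no baseline infectiousness and names no test, so power at fewer feeds cannot be computed from the document. What can be said is that the claim depends on feeds that are not assured.

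**What to change.** In the B3 sample size answer:

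1. Replace *at least 28%* with *about 28%, assuming the two effects are independent*.
2. State the assumed share of carriers who will be bled and fed, and use it consistently across arms.
3. Replace the promise to ensure at least 30 feeds with the feeds expected over illustrative carriage rates. For 200 children, rates of 10%, 15%, 20%, 28% and 40% give 20, 30, 40, 56 and 80 carriers, to be multiplied by the stated yield. Label these rates as assumptions, not bounds.
4. Make the SP versus SP + CQ power claim explicitly conditional on reaching the feed target.
5. Use one minimum feed target; B3 now gives both 25 and 30.

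The cost is a rewrite of one paragraph. Enrolment, treatment and procedures need not change. The stated assurance on feeds and power becomes less favourable.
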